### **Statistical Analysis**

In univariate analyses, the percent change from baseline will be compared across intervention arms using appropriate parametric (ANOVA, *t* tests) or non-parametric (Wilcoxon) methods.

In multivariate analyses, change in outcomes will be modeled using linear regression. Percent change from baseline will be a continuous outcome with intervention arm as the predictor of interest and various participant characteristics as covariates (e.g. sex, age, race/ethnicity, anthropometry, self-reported diet and exercise, pharmacotherapy, family history, etc.). Repeated measures analysis using the outcome at different time points and mixed-effects models will also be performed. Available nonparticipants will serve as contemporaneous comparators to address possible secular trends in outcome values.

Study participants in the exercise program may also be undergoing concomitant pharmaceutical therapy to reduce HbA1c. The approach is to repeat the above analyses stratified by use of hypoglycemic medication. Another approach is to use a composite binary outcome variable for whether participants were successful in either decreasing diabetes medication or reduced HbA1c by 0.5% without increasing medications. Logistic regression will be used to assess the likelihood of achieving the composite outcome.

Study participants will be studied based on their randomized assignment (intention-to-treat). In sensitivity analyses, participants may be re-analyzed based on actualized attendance if they more closely resemble one of the other arms (once-weekly, thrice-weekly, usual care). A study participant assigned to thrice-weekly, who attends only once a week may be re-analyzed as a weekly patient. Stratification by adherent (attendance >80%) or not will also be another sensitivity analysis.

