### 1.1.b BACKGROUND

Type 2 diabetes (T2DM) affects 25.8 million people in the United States and the prevalence and incidence is increasing. Research has shown that physical activity is beneficial in T2DM management with lower glycemic control achieved when patients follow a structured exercise program in a research setting. Given the known benefits of dietary changes in T2DM, nutrition referrals are common in current clinical practice. Despite the similarly known benefits of exercise, physical activity referrals are not readily available in the clinical setting. According to the current American Diabetes Association (ADA) guidelines, individuals with T2DM should engage in at least 150 minutes of moderate-intensity aerobic activity per week and resistance exercises at least 2 times per week. However, approximately 38 percent of T2DM patients do not exercise at recommended levels and 31 percent do not exercise at all.

A recent meta-analysis of randomized controlled trials (RCTs) demonstrated that highly structured physical activity training regimens were effective in reducing glycosylated hemoglobin A1c (HbA1c) levels in individuals with T2DM, while physical activity advice alone had no effect on HbA1c. Of the 23 RCTs which tested structured training programs, most consisted of at least three structured sessions per week, and ranged in length from 3 – 12 months. While the efficacy of such intensive physical activity interventions among individuals with T2DM in a highly structured research setting has been proven, practical approaches to translate and extend these findings into the clinical setting are needed. Less intensive approaches, such as physical activity advice delivered by physicians, have been tested in clinical settings, and are not effective in increasing physical activity.

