## 2.4.c INCLUSION AND EXCLUSION CRITERIA

The purpose of establishing inclusion and exclusion criteria is to define the participant population to be used for the research study. In order for a potential participant to become an eligible participant in the IMPACT study, he or she must meet all of the final eligibility criteria:

- Has primary care physician at SHC
- Diagnosed with Type 2 diabetes
- HbA1c between 6.6 and 9.9%
- Between 30 to 65 years of age
- Has ability to communicate with study staff, sign informed consent, and accept randomization
- Free of intervening events (ie. a sick spouse)
- Willing to exercise at Cardiac Therapy Foundation (CTF) up to three times a week for six months
- Willing to attend all study visits

The IMPACT study has also defined criteria that would exclude an individual from becoming eligible for the study. The criteria for study exclusion are:

- Insulin-dependent
- Resting heart rate  $\geq 120$  beats per minute (bpm)
- Blood pressure  $\geq 180/100$  mm Hg
- History of or present heart or cardiovascular problems
- History of or present respiratory disease
- History of or present spinal cord injury
- History of stroke or Transient Ischemic Attack (TIA)
- History of cancer diagnosis in the past 5 years or present cancer diagnosis
- Medical, psychiatric, behavioral limitations that may interfere with study participation
- Participating in other clinical trials that may interfere with study procedures and outcomes
- Currently pregnant or plans to become pregnant within three years
- Plans to be away more than four weeks in the next nine months
- Plans to leave the community within five years

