#### ***Modifiable Activity Questionnaire***

Modifiable Activity Questionnaire (MAQ) assesses physical activity levels. The potential participant is asked to recall the types, frequency, and duration of engaged exercise activities for the past three months. MAQ also evaluates sedentary levels through its supplemental questions.

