## **STUDY AIM 1: CLINICAL EFFECTIVENESS**

### **Research Questions**

1. Does a thrice-weekly, structured exercise regimen have greater reduction in HbA1c than a weekly contact exercise regimen? How do these interventions compare to usual care?
2. Are the same improvements observed for process measures (i.e., VO2 max and self-reported physical activity)?

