### **Primary Outcomes and Process Measures**

Primary outcomes and process measures will be compared between the three intervention arms (weekly, thrice-weekly, usual care). Primary outcomes include absolute change in percent HbA1c, and process measures include change in VO2 max and self-reported physical activity. Adherence will be defined as attending more than 80% of assigned structured exercise sessions, and will be used as a covariate for stratification or adjustment.

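### Percent change from baseline, set for the Aim 1 comparison and regression with no exemption, is undefined for self-reported physical activity when the baseline is zero

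*Protocol*

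**What the plan says.** In section 6.2.a, Study Aim 1, the heading Primary Outcomes and Process Measures defines the HbA1c outcome as an absolute change. For the others it says that "process measures include change in VO2 max and self-reported physical activity". All are compared across the three arms, and the second Aim 1 research question asks specifically about the process measures.

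The Statistical Analysis text that follows uses another scale, twice:

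- "In univariate analyses, the percent change from baseline will be compared across intervention arms using appropriate parametric" or non-parametric methods, the Wilcoxon test being named.
- For the linear regression: "Percent change from baseline will be a continuous outcome with intervention arm as the predictor of interest".

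Neither sentence exempts an outcome or says what to do with a zero baseline. The same paragraph adds: "Repeated measures analysis using the outcome at different time points and mixed-effects models will also be performed".

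Activity is measured with the MAQ (section 3.2.b), which asks participants to "recall the types, frequency, and duration of engaged exercise activities for the past three months". The only eligibility criterion about exercise (section 2.4.c) concerns the future: "Willing to exercise at Cardiac Therapy Foundation (CTF) up to three times a week for six months". Section 1.1.b reports that "approximately 38 percent of T2DM patients do not exercise at recommended levels and 31 percent do not exercise at all".

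**The concern.** Percent change divides by the baseline value. HbA1c cannot be zero, and entry requires 6.6 to 9.9%. VO2 max cannot be zero either. Reported exercise can be, and nothing in the entry criteria prevents it. A participant who goes from no exercise to regular exercise is the clearest success this trial could record, yet has no value on the specified scale. A participant who starts just above zero gets a very large value that can dominate a mean or a least-squares fit.

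The activity comparison would then describe only participants who were already active to some degree. That fits poorly with the section's commitment to analyse people as randomised. It also leaves the analyst to choose a workaround after seeing the data, such as dropping zeros or adding a constant. Activity is part of the primary hypothesis in section 2.3.a, although sections 2.1.d and 6.2.a class it as a process measure.

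Separately, the scale in the analysis text does not match the definitions just above it, for HbA1c as well as for activity.

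**Working it through.** **1. Trial size (section 6.2.b).** 92 per arm / (1 − 0.20) = 115 per arm, and 3 × 115 = 345. This reproduces the protocol's total. After attrition, 3 × 92 = 276 remain.

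**2. The scale.** Percent change = 100 × (follow-up − baseline) / baseline. At baseline 0 the denominator is zero. A move from 0 to a positive value has no finite result, and 0 to 0 is 0/0.

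**3. Instability near zero.** Take the same gain of 120 min/week from different baselines (the gain and the baselines are illustrative):

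| Baseline (min/week) | Percent change |
|---|---|
| 150 | 120/150 = 80% |
| 60 | 120/60 = 200% |
| 10 | 120/10 = 1200% |
| 0 | undefined |

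**4. How many could be lost.** The protocol gives no baseline activity distribution for this trial. The 31% is its background figure for patients with type 2 diabetes; the other shares are assumptions.

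| Share at zero | Of 345 randomised | Of 276 after attrition |
|---|---|---|
| 10% | 34.5, about 35 | 27.6, about 28 |
| 20% | 69 | 55.2, about 55 |
| 31% | 106.95, about 107 | 85.56, about 86 |
| 40% | 138 | 110.4, about 110 |

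At 31% this is 0.31 × 115 = 35.65, about 36 per arm as randomised.

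**5. Could there be no zeros at all?** If only 2% of participants had a zero baseline, the chance of none among 345 would be 0.98^345 = 0.0009, about 0.1%. Some undefined values should be expected even if the trial population is far more active than the background figure suggests.

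**6. The alternative scale.** Absolute change is follow-up − baseline, which is defined at zero. In a linear model with arm and baseline as predictors, replacing the follow-up value by absolute change lowers the baseline coefficient by exactly 1 and leaves the arm effect unchanged. Either response gives the same treatment comparison, and neither loses anyone because of a zero baseline.

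**The case against.** Several points on the other side have weight.

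- **The analysis text does not name physical activity.** The percent-change sentences may have been drafted with HbA1c in mind. That is possible, but they exempt nothing, and HbA1c is itself defined as an absolute change, so the mismatch remains on either reading.
- **Other analyses are planned.** The repeated-measures and mixed models use the outcome at each visit. On the natural reading they need no ratio to baseline and keep participants with a zero baseline. This stands, and it confines the problem to the univariate comparison and the linear regression. A reader might infer that the research question on process measures cannot be answered; the protocol does not support that.
- **A rank test is allowed.** Wilcoxon limits the pull of extreme values in the univariate comparison. It does not rank 0/0 without a rule, and it does nothing for the regression.
- **The 31% is not about this trial.** It describes patients in general, with no stated definition or recall period. Participants here are volunteers prepared to exercise, and a zero MAQ score means no reported activity over three months. A reader might infer that 31% of participants would be lost; the documents do not show this.
- **Details may sit in a statistical analysis plan.** A zero-baseline rule is commonly left to that document, which is not shown. Here, however, the protocol has itself fixed the unsuitable scale.
- **The main result is untouched.** Aim 1 is sized on HbA1c, which has no zero-baseline problem. Also, exclusion on a baseline value need not bias the contrast between arms; the harm is that the inactive group is removed.

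**Conclusion.** The point holds for two analyses of one measure. As written, the univariate comparison and the linear regression of self-reported physical activity have no defined value for participants with a zero MAQ baseline, and are unstable near zero. The number affected is unknown: about 107 of 345 if the background 31% applied, and 35 to 138 across an assumed 10% to 40%. The conclusion rests on reading the percent-change sentences as covering every Aim 1 measure, which is what they say, and on the MAQ score being able to reach zero, which its description and the entry criteria allow. That the analysis text and the outcome definitions disagree on scale is certain on any reading.

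Zero baselines do not touch the HbA1c or VO2 max results, or the mixed models. The wording should be corrected before analysis, but this is not a threat to the trial's main conclusion.

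**What to change.** In section 6.2.a, Study Aim 1, Statistical Analysis:

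1. For self-reported physical activity, replace percent change by absolute change, or by the follow-up value, with baseline MAQ activity as a covariate. Name a rank-based or transformed version to be used if the data are skewed. State that no participant with follow-up is excluded because of a zero baseline.
2. Align the scale for all Aim 1 measures with the definitions under Primary Outcomes and Process Measures: absolute change for HbA1c, and a stated form of change for the process measures.

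The cost is a sentence or two of wording. No new data are needed, because the schedule in section 4.1.b already collects the MAQ before randomisation and at every follow-up visit. The change keeps participants with a zero baseline; it does not recover those lost to attrition. A yes/no outcome for reaching the 150 min/week aerobic recommendation could be added, but it is optional and would add to the number of tests.

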## **Chapter 6: Randomization and Data Analysis Plan**

## 6.1 RANDOMIZATION

### 6.1.a RANDOMIZATION

Block Randomization is the method to be used to randomize study participants into study arms. The method is developed to pre-specify the number of arm assignments in a random order. IMPACT will utilize Block Randomization in conjunction with stratification in order to promote balance of participant characteristics within each study arm. The participant characteristics, or parameters, to be used for the IMPACT study includes: (1) age, (2) gender, and (3) HbA1c level.

Participant characteristics will be stratified as followed:

- Age (years)
  - >29.9 – 50.9 (young age)
  - 51.0 – 65.0 (older age)
- Gender
  - Male
  - Female
- HbA1c (percentage)
  - 6.6 – 7.9 (low A1c)
  - 8.00 – 9.9 (high A1c)

As a result, there are eight (8) strata in total:

1. Low HbA1c, younger age and female
2. Low HbA1c, younger age and male
3. Low HbA1c, older age and female
4. Low HbA1c, older age and male
5. High HbA1c, younger age and female
6. High HbA1c, younger age and male
7. High HbA1c, older age and female
8. High HbA1c, older age and male

Each block size will contain six (6) group assignments, evenly distributed across the three study arms. The blocks will contain random permutations (ie. 211332, 321231, etc) that are pre-determined by SAS.

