#### **SUB-GROUP ANALYSES**

Analyses will be performed within sub-groups to compare the primary outcome of absolute change in percent HbA1c and process measures of changes in VO2max and self-reported physical activity:

1. Years of age at study enrollment. 30-45 vs. 45-55 vs. 56-65
2. Gender. Male versus female.
3. Race. White vs. African American/Black vs. American Indian vs. Asian vs. Pacific Islander vs. Other
4. Ethnicity. Non-Hispanic/Latino vs. Hispanic/Latino

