## **6.2.b POWER AND SAMPLE SIZE**

The primary analyses for this study will be comparing the clinical outcomes, patient-centered outcomes, and cost effectiveness of structured exercise regimens across varying frequencies (once vs. thrice-weekly, compared to usual care). For Specific Aim 1, overall change in baseline of outcome values will be examined (e.g. HbA1c, VO2max, physical activity). By the algebraic properties of log and variance, we estimated difference in groups as  $\log(\text{HbA1c}_1) - \log(\text{HbA1c}_2) = \log(\text{HbA1c}_1 / \text{HbA1c}_2)$ , and  $\text{SD}(\log(\text{HbA1c})) = \text{SD}(\text{HbA1c}) / \text{mean}(\text{HbA1c})$ . A two-sample *t*-test between means, Bonferroni adjusted  $\alpha = 0.05/3 = 0.016$ , assuming normality of  $\log(\text{HbA1c})$ , equal group variances, and a baseline mean HbA1c of 6.5%, we will have 80% power to detect a 0.5% point difference in HbA1c with 92 patients/arm. Accounting for a 20% attrition, this will require 115/arm, 345 patients total.

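### The primary outcome is absolute change in HbA1c, but the planned tests and regression use percent change, and baseline HbA1c is not named as a covariate

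*Protocol*

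**What the plan says.** Section 6.2.a, Study Aim 1 (Primary Outcomes and Process Measures) gives the definition: "Primary outcomes include absolute change in percent HbA1c". The Sub-group Analyses paragraph agrees and says they will "compare the primary outcome of absolute change in percent HbA1c".

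The Statistical Analysis paragraph of the same aim changes scale. In the univariate step (ANOVA, t or Wilcoxon tests), "the percent change from baseline will be compared across intervention arms". In the regression step, "Percent change from baseline will be a continuous outcome with intervention arm as the predictor of interest and various participant characteristics as covariates". The covariates are an open list of examples: "e.g. sex, age, race/ethnicity, anthropometry, self-reported diet and exercise, pharmacotherapy, family history, etc". Sex and age are in it; baseline HbA1c is not. Repeated-measures and mixed-effects models are added without saying how baseline enters them. No analysis is named as primary.

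Section 6.2.b uses logarithms: "By the algebraic properties of log and variance, we estimated difference in groups as" the log of the HbA1c ratio, with the target stated as 0.5 percentage points and 92 evaluable patients per arm.

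Section 6.1.a stratifies the randomisation: "The participant characteristics, or parameters, to be used for the IMPACT study includes: (1) age, (2) gender, and (3) HbA1c level". Section 3.2.b has HbA1c measured by fingerstick in every candidate at the baseline visit.

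**The concern.** The defined outcome, the analysed outcome and the planning target should be one quantity. Here an analyst who follows the Statistical Analysis paragraph reports a difference in mean percent change. That estimate cannot be set against the 0.5-point target and is not the outcome the protocol defines. Percent change also weights patients by their baseline: the same fall in points counts for more in a patient who starts low.

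The second issue is efficiency. Baseline HbA1c is usually the strongest predictor of later HbA1c, and the design already treats it as important enough to stratify on. The univariate tests use it only as the subtracted or dividing value, and the regression does not commit to it. Nor does the text commit to age and sex, which appear only as examples.

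**Working it through.** **1. The scales side by side**

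| Place in the protocol | Quantity |
|---|---|
| 6.2.a, Primary Outcomes; Sub-group Analyses | absolute change, HbA1c points |
| 6.2.a, Statistical Analysis (tests and regression) | percent change from baseline |
| 6.2.b, Power and Sample Size | difference in log HbA1c, target 0.5 points |

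**2. The scales are not interchangeable.** A 0.5-point fall, over the eligible range in Section 2.4.c (6.6 to 9.9):
- 0.5/6.6 = 7.6%
- 0.5/8.0 = 6.25%
- 0.5/9.9 = 5.1%

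**3. The plan's own figure.** Section 6.2.b gives alpha 0.016 (0.05/3), 80% power and a mean of 6.5, but no SD, so 92 cannot be reproduced from stated inputs alone. Assume SD 1.0 and a two-sided test. The effect is log(7.0/6.5) = 0.0741 and the SD of log HbA1c is 1.0/6.5 = 0.154. The two-sample t calculation then gives 92 per arm (power 0.805). The attrition step follows: 92/0.80 = 115, and 3 × 115 = 345. So 92 is consistent with the SD of a single HbA1c value. With equal SDs at both visits, a change score has variance 2(1−r) times that of a single value, which equals it only when the correlation r is 0.5.

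**4. Baseline adjustment: variances.** Assume SD 1.0 and mean 7.6 before the entry window is applied, and let r be the correlation before the window. Restricting baseline to 6.6–9.9 reduces its SD to about 0.75 (variance 0.56). Among enrolled patients:
- unadjusted absolute change: (1−r²) + (1−r)² × 0.56
- ANCOVA: 1−r²

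| r | Change | ANCOVA | Ratio | Ratio without the window |
|---|---|---|---|---|
| 0.3 | 0.91 + 0.27 = 1.18 | 0.91 | 0.77 | 0.91/1.40 = 0.65 |
| 0.5 | 0.75 + 0.14 = 0.89 | 0.75 | 0.84 | 0.75/1.00 = 0.75 |
| 0.7 | 0.51 + 0.05 = 0.56 | 0.51 | 0.91 | 0.51/0.60 = 0.85 |

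**5. Baseline adjustment: power.** Simulation with 20,000 trials per row, 92 per arm, two-sided alpha 0.05/3 and a true effect of 0.5 points. Baseline is Normal(7.6, 1) restricted to 6.6–9.9, and follow-up is regressed on baseline with slope r and residual variance 1−r².

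| r before window | r among enrolled | Absolute change | Percent change | Log ratio | ANCOVA |
|---|---|---|---|---|---|
| 0.3 | 0.23 | 75.5% | 77.4% | 77.7% | 86.9% |
| 0.5 | 0.40 | 88.0% | 89.0% | 89.3% | 93.2% |
| 0.7 | 0.59 | 98.1% | 98.3% | 98.3% | 98.8% |

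The three unadjusted scales lie within about 2 points of each other, and their significance decisions differed in 4.4%, 2.6% and 0.5% of trials. Moving from percent change to ANCOVA gains 9.5, 4.2 and 0.5 points. The decision changed in 12.4%, 5.8% and 0.8% of trials.

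**6. Sensitivity.** If the correlations are instead imposed among enrolled patients with follow-up SD 1.0 (underlying mean 7.5, alpha 0.016), percent change versus ANCOVA is 80% vs 87% at 0.3, 91% vs 93% at 0.5 and 99% vs 99% at 0.7.

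**The case against.** The best defence has four parts.

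- **The outcome is defined only once.** The log scale in Section 6.2.b is a planning device with a target in points, and no analysis is committed to it. This stands. The real conflict is between an absolute definition and a relative analysis. A reader might infer three rival primary outcomes with three competing P values, but the text does not go that far, and the simulated decisions seldom differ.
- **Percent change may be loose wording for change in a quantity measured in percent.** This is possible for HbA1c. But the same sentences also cover VO2 max and physical activity, where that reading does not work, and the wording would need correcting in any case.
- **The covariate list is open, names age and sex, and is followed by mixed models; an SAP may fix the rest.** This stands in part: nothing excludes baseline HbA1c, and leaving details to an SAP is no fault. An SAP cannot, however, follow both the definition and the analysis as written, and an example list that leaves out a stratification factor is a poor starting point for it.
- **The power gain rests on an SD, a mean and a correlation that the protocol does not give.** This stands, and at high correlation the gain is negligible.

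A reader might also infer that the mismatch of scales itself wastes power, or that the narrow entry range makes the loss from omitting baseline worse. Neither holds. The scales have nearly equal power. The entry window brings the variance ratio closer to 1 (0.65 to 0.77 at r = 0.3), so it shrinks the penalty. Nor can one conclude that the trial falls short of 80% power: that depends on the unstated inputs.

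**Conclusion.** The mismatch is established from the text alone: the outcome is defined in HbA1c points, tested and modelled as percent change, and sized through logarithms for a target in points. The consequence is an effect estimate that cannot be read against the definition or the 0.5-point target. There is no material loss of power from the scale as such.

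The omission of baseline HbA1c from the named covariates is a weaker but worthwhile point. Adjusting for it gains about 10 points of power at a pre-window correlation of 0.3 (0.23 among enrolled patients), about 4 at 0.5 and about 1 or less at 0.7. These figures assume SD 1.0, mean 7.6, 92 per arm, alpha 0.05/3 and the 6.6–9.9 entry window. The direction is secure; the size is not. No separate gain is claimed for age and sex. The plan should be corrected, with high confidence on the scale mismatch and moderate confidence on the benefit of adjustment.

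**What to change.** - In Section 6.2.a, Statistical Analysis, make HbA1c in percentage points the single primary scale, in line with the outcome definition and the Sub-group Analyses paragraph.
- Name one primary model: ANCOVA, or a repeated-measures model that includes baseline, with arm, continuous baseline HbA1c, age and sex. Report adjusted differences in HbA1c points.
- Move percent change and the unadjusted ANOVA, t and Wilcoxon tests to sensitivity analyses.
- Restate Section 6.2.b on the same scale, giving the SD and the assumed baseline-to-follow-up correlation.

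The cost is wording only. Baseline HbA1c, age and sex are all known before randomisation, because the strata need them, and no extra data or visits are required.

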#### 4.1.c EXERCISE INTERVENTION MEASUREMENTS

Additional measurements will be collected from study participants specifically in the exercise intervention groups (Arm 1 and Arm 2). The following is a list of essential measurements to be collected over the course of the six-month exercise intervention period.

- Blood glucose control
  - Daily blood glucose levels
- Physical fitness
  - Strength
  - Exercise intensity
- Physical activity level
  - Activity type
  - Activity duration
  - Activity intensity
  - Activity location
- Resource utilization
  - Participant attendance
  - Staff presence

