### **Equipment**

All equipment required for the group exercise sessions are provided by CTF or the IMPACT study. Equipment includes free weights (dumbbells), cardio machines (bikes) and resistance bands. The IMPACT Study will provide additional equipment, such as glucometers, heart monitors, and fast-acting carbohydrates (snack, juice, glucose tablets).

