## **6.2 DATA ANALYTICAL METHODS**

### **6.2.a DATA ANALYSIS PLAN**

Statistical analyses will investigate clinical effectiveness of structured physical activity regimens across varying frequencies. The main statistical approach will be to date-match outcomes to concomitant exercise regimens, then to examine univariate and multivariate associations with changes in clinical outcomes, patient-centered outcomes, and cost. Statistical significance will be determined at  $P < 0.01$ , a stricter value due to the expected number of models used, or with other adjustments for multiple comparisons when applicable. Statistical analyses will be performed using SAS® (Cary, NC), and supplemented with STATA or Splus for methods not available in SAS®.

Study participants who are not able or willing to continue with the randomized frequency of intervention will be treated as loss to follow-up and only data obtained while in the assigned protocol will be used in the primary analysis (intention-to-treat). Since participants and non-participants continue to receive care within the healthcare system contemporaneously during the research study, IMPACT will obtain interstitial outcome data and complete clinical narrative through observational data available in the EHR. The statistical analysis will be conducted by Senior Statistician/s with the guidance of Biostatistical Consultant [name].

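### The supporting Aim 1 composite counts any diabetes-drug reduction as success with no HbA1c condition, so a drug cut followed by an HbA1c rise is scored as success

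*Protocol*

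**What the plan says.** Section 6.2.a, Study Aim 1, Statistical Analysis, recognises that participants may also be on drugs that lower HbA1c. It proposes to repeat the analyses stratified by use of such drugs, and then adds: "Another approach is to use a composite binary outcome variable for whether participants were successful". Success means being "successful in either decreasing diabetes medication or reduced HbA1c by 0.5% without increasing medications", and the composite is analysed by logistic regression. Pharmacotherapy also appears in the same section among the regression covariates.

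The composite is not the primary endpoint. Under Primary Outcomes and Process Measures the text reads: "Primary outcomes include absolute change in percent HbA1c". The general significance level in 6.2.a is P<0.01, described as "a stricter value due to the expected number of models used, or with other adjustments for multiple comparisons when applicable".

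No other section puts a condition on the medication limb. Section 6.2.a does expect a "complete clinical narrative through observational data available in the EHR", but the success rule does not refer to it. HbA1c is scheduled at all six visits (table in 4.1.b).

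**The concern.** The purpose of the composite is to stop drug changes from distorting the reading of glycaemic benefit. It closes one route: a fall in HbA1c does not count if drugs were increased. It leaves the mirror route open: a drug reduction counts even if glycaemic control is lost afterwards. Attaching the no-increase condition to both limbs would not help, because it would still place no HbA1c condition on a drug cut.

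What is at stake is a supporting result. If cuts followed by a rise are more frequent in the exercise arms, the composite overstates the benefit of exercise. If they are equally frequent in all arms, it blurs a real difference.

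**Working it through.** **Step 1: apply the rule as written.** The table crosses three medication changes with three HbA1c changes (in percentage points). It compares the stated rule with one that also requires, for the medication limb, that HbA1c has not risen.

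| Medication | HbA1c change | Stated rule | With guard |
|---|---|---|---|
| down | -0.6 | success | success |
| down | 0.0 | success | success |
| down | +0.8 | **success** | **failure** |
| same | -0.6 | success | success |
| same | 0.0 | failure | failure |
| same | +0.8 | failure | failure |
| up | any of the three | failure | failure |

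Of the nine combinations, exactly one changes class. Under the stated rule a rise of 0.8 is a failure if the drug is unchanged and a success if the drug was cut.

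**Step 2: size if such cuts favour the exercise arms.** The protocol states no power, sample size or event rate for the composite, so there is no figure of its own to reproduce. Inputs:

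- n = 92 evaluable per arm (6.2.b). The inflation there checks: 92/0.80 = 115 per arm, and 3 × 115 = 345.
- Significance level 0.01 (6.2.a).
- Assumed: base success p0 = 0.30 in both arms, no true effect.
- Assumed: a share r = 2.5% to 7.5% of the remaining Arm 2 participants has a cut followed by a rise, and none does in usual care.

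Formulas: p2 = p0 + (1 - p0) × r, and OR = [p2/(1 - p2)] / [p0/(1 - p0)]. Rejection is from a likelihood-ratio test of two proportions, by exact enumeration of both binomials.

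| r | p2 | OR | Rejection at 0.01 |
|---|---|---|---|
| 0 | 0.300 | 1.00 | 1.1% |
| 2.5% | 0.30 + 0.70 × 0.025 = 0.3175 | 0.4652/0.4286 = 1.09 | 1.3% |
| 5% | 0.30 + 0.70 × 0.05 = 0.335 | 0.5038/0.4286 = 1.18 | 2.1% |
| 7.5% | 0.30 + 0.70 × 0.075 = 0.3525 | 0.5444/0.4286 = 1.27 | 3.7% |

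Base success changes the odds ratio modestly. At p0 = 0.20 and r = 7.5%, p2 = 0.26 and OR = 0.3514/0.25 = 1.41. At p0 = 0.40 and r = 2.5%, p2 = 0.415 and OR = 0.7094/0.6667 = 1.06.

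For scale, start from 28/92 in both arms. With 45/92 in one arm P = 0.0101, and with 46/92 P = 0.0066. So 18 extra successes are needed, which is 18/64 = 28% of the non-successes and far above the assumed range.

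**Step 3: size if such cuts are equally common in all arms.** Assume true success of 20% against 40%, 92 per arm, and two-sided alpha 0.016 (the level used in 6.2.b). Let a share m of the remaining participants in each arm be scored as success only through a drug cut.

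| m | Observed success | Difference | Power |
|---|---|---|---|
| 0 | 20% vs 40% | 20 points | 71% |
| 5% | 24% vs 43% | 19 points | 63% |
| 10% | 28% vs 46% | 18 points | 55% |

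**The case against.** **A drug cut can be a real benefit.** If exercise lowers glucose enough to prompt a cut, it is acting on glycaemia, and calling every such cut an error would be wrong. This stands, and it limits the point to cuts followed by a rise. A reader might instead charge all low-glucose cuts to the rule. At 5% to 15% of the remaining Arm 2 participants that gives odds ratios of 1.18 to 1.59 and rejection of 2.1% to 14.3%. Those figures include cuts after which HbA1c did not rise, so they do not measure this defect. If half of the cuts are followed by a rise, the share is the 2.5% to 7.5% used above.

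**The direction is not established.** A reader might infer that the composite is biased towards exercise, since "Daily blood glucose levels" are listed only for Arms 1 and 2 (4.1.c) and fast-acting carbohydrate is supplied for the sessions (4.2.a, Equipment). That is plausible but not shown. Section 4.1.c says where glucose data are collected, not who tests. The exercise stress test paragraph in 3.2.b expects candidates for every arm to have their own glucometer. Insulin-dependent patients are excluded. Carbohydrate treats a low on the spot and is no evidence of a drug cut. Usual care continues ordinary diabetes management, so zero such cuts there is an extreme assumption. If usual care had half the Arm 2 rate, success would be 0.30875 vs 0.3175 up to 0.32625 vs 0.3525, with odds ratios of only 1.04 to 1.12.

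**It is one supporting approach among several, and only sketched.** Stratification by drug use and the pharmacotherapy covariate also address the problem, and a SAP could complete the definition. This limits the consequence. It does not remove the point, because the either/or rule is stated, not left open.

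**Conclusion.** The point holds as a flaw in a stated definition: the medication limb has no HbA1c condition, and the protocol adds none elsewhere. That conclusion needs no assumption about rates.

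The consequence is small and confined to a supporting analysis. Under the assumptions in the working, the odds ratio with no true effect is 1.09 to 1.27 and rejection at P<0.01 rises from 1.1% to between 1.3% and 3.7%. An inflated estimate is thus likelier than a false significant result. The effect shrinks if usual care also has such cuts, and becomes dilution if the arms are equal. Every rate here is assumed.

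A reader might infer that the trial's main conclusion is at risk. The documents do not support that: the primary outcome is the change in HbA1c itself, and it would be reported beside the composite.

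**What to change.** In 6.2.a, Study Aim 1, Statistical Analysis, define success as either:

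- (a) a reduction in diabetes medication with HbA1c at the same visit not above baseline, or within a margin set by the sponsor's clinicians; or
- (b) a fall in HbA1c of at least 0.5 percentage point with no increase in diabetes medication.

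The cost is one sentence. HbA1c is already measured at every visit, so no visit or test is added. The downside is slightly fewer successes in this supporting analysis.

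Recording the reason for each drug change, with a sensitivity analysis that leaves out cuts made for low glucose, is optional and not needed for the fix. Deciding that a cut was made to prevent a low is subjective, and participants know their arm, so that analysis could bring a bias of its own.
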